### Outcome measures and data collection

The primary outcome measure is glycosylated haemoglobin (HbA1c). Secondary outcome measures are self-rated quality of life and diabetes symptoms. Explanatory outcome measures include blood pressure, lipid profile, body weight, waist circumference, insulin resistance and beta-cell function estimates, and physical fitness. All outcome measures are collected at baseline and at follow-up visits after 6, 12 and 24 months.

At every visit, biochemical, anthropometrical, physiological and physical values are obtained. The same investigator measures the anthropometrical and the physiological outcomes throughout the study. Physiotherapists at the health care centre and at the outpatient clinic complete the physical tests. The patients fill in two self-administered questionnaires on quality of life and diabetes related symptoms at each visit.

### Anthropometrical measurements

Weight (kg) is measured without shoes in indoor clothing and the same equipment will be used throughout the study. Height (cm) without shoes is only measured at baseline.

Waist circumference (cm) is measured at a level midway between the lower rib margin and iliac crest with the subjects standing without clothes on and with relaxed breathing.

### Physiological measurements

Electrocardiogram (ECG) is recorded at baseline. Blood pressure is measured on both arms are done using an aneroid manometer with the patient in a sitting position after 10–15 minutes of relaxed conversation. The mean of 3 consecutive measurements is used for each arm. Patients' target blood pressures are at the recommended goal of 130/80 mmHg defined according to the European guidelines [26].

Biothesiometry of the pulp on the first toe on both feet's is used for quantitative assessment of peripheral neuropathy. The patients will be tested by increasing the amplitude from zero and then the patients will indicate when they feel the vibration. The cut-off point for ulcer risk is > 25 volts [27].

### Biochemical measurements

Blood and urine samples are taken in the morning after an overnight fast. Plasma glucose, lipids, C Reactive Protein, creatinine and urine albumin/creatinine ratio are analysed at the Department of Clinical Biochemistry, Bispebjerg University Hospital. Haemoglobin A1c is measured on venous whole blood samples in K2-EDTA tubes at the Department of Clinical Biochemistry, Steno Diabetes Centre [28]. Blood samples for serum C-peptide, insulin and proinsulin are centrifuged for 10 min at 3000 rpm, at 20°C immediately after sampling, and serum is isolated and frozen before analysis at the Steno Diabetes Centre. Blood samples for later analyses will be centrifuged within 60 minutes of sampling and stored frozen at -20°C. The target for haemoglobin A1c is below 6.5% according to international guidelines [27].

The Homeostasis Model Assessment (HOMA) is used to estimate insulin resistance and beta-cell function [29]. HOMA-IR is computed as follows: fasting insulin (μU/ml) × fasting glucose (mmol/L)/22.5. HOMA-B is calculated using the following formula: 20 × fasting insulin (μU/ml)/fasting glucose (mmol/L) – 3.5.

Microalbuminuria is defined as a urine Albumin:Creatinine Ratio (ACR) ≥ 2.5 – 25 mg/mmol in men and ≥ 3.5 – 25 mg/mmol in women [30]. Treatment targets for blood lipids are values of fasting total cholesterol below 4.5 mmol/L and fasting LDL cholesterol below 2.5 mmol/L [31].

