### Sample size considerations and statistical methods

The size of the study population is based on the primary outcome measure HbA1c and is estimated on the basis of the results of two meta-analyses relating to education and exercises in T2DM patients [8,14]. According to power calculation, an absolute difference of 0.7% in HbA1c between the groups (power 0.9, significance level 0.05) may be detected with 80 patients in each group. This calculation is based on a standard deviation of the HbA1c-value of 1.3 from larger population studies [40].

Neither patients nor study personnel are blinded to treatment assignment. The study statistician carrying out the data analysis on the primary and secondary outcomes will be blinded and will not have any contact with the patients.

Descriptive statistics (means ± SD, or median and interquartile ranges, as appropriate) will be used to describe the study sample with regards to baseline characteristics. The analysis will be performed according to the intention-to-treat principles using the statistical software SAS 9.1. Comparisons of primary and secondary outcomes between the two groups will be analyzed by values after the intervention at the 6 months follow-up visit, and 12 and 24 months after baseline, using appropriate parametric tests for variables fulfilling the normal distribution criteria or appropriate non-parametric tests for variables not fulfilling the normal distribution criteria. Sensitivity analyses will be carried out with adjustment for possible confounders. When relevant the change in outcomes from baseline to 6, 12 and 24 months follow-up will be assessed. The proportion of patients reaching the recommended goals for glycated haemoglobin, blood pressure and lipids will be compared in a sub-analysis. Statistical significance is set at P < 0.05.

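### The HOMA-B formula lacks brackets around glucose minus 3.5; computed as printed, beta-cell function comes out roughly 30% to 75% too low, in an explanatory outcome only

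*Protocol article*

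**What the plan says.** Under Biochemical measurements the protocol article says that the Homeostasis Model Assessment is used to estimate insulin resistance and beta-cell function, cites a source for the method, and gives both formulas in running text. The first reads: "HOMA-IR is computed as follows: fasting insulin (μU/ml) × fasting glucose (mmol/L)/22.5". The second reads: "HOMA-B is calculated using the following formula: 20 × fasting insulin (μU/ml)/fasting glucose (mmol/L) – 3.5".

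No other part of the article gives a bracketed version of the second formula or a worked HOMA-B value.

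The role of the variable is set under Outcome measures and data collection: "Explanatory outcome measures include blood pressure, lipid profile, body weight, waist circumference, insulin resistance and beta-cell function estimates, and physical fitness". The same section schedules all outcome measures at baseline and at 6, 12 and 24 months. HbA1c is the primary outcome; quality of life and diabetes symptoms are secondary.

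**The concern.** Read by the usual order of operations, the HOMA-B formula is (20 × insulin / glucose) − 3.5. A constant of 3.5 sits naturally beside a glucose in mmol/L. Taken from a ratio of insulin to glucose it has no evident meaning. The likely intention is 20 × insulin / (glucose − 3.5).

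The two forms give different quantities. If an analyst programs the formula as printed, every HOMA-B value at every visit is too low. The discrepancy is not a constant factor, so it need not cancel in a change from baseline or in a comparison of arms. The programme is meant to improve glycaemic control, so glucose is expected to move differently in the two arms, and the error would move with it.

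**Working it through.** **Inputs.** Both formulas come from Biochemical measurements. Write I for fasting insulin (μU/ml) and G for fasting glucose (mmol/L). The article states no values of I or G, so every value below is an assumption. It also states no HOMA-B figure, so there is none to reproduce.

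**Step 1: the two readings.**

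- As printed: P = 20 × I / G − 3.5
- Bracketed: B = 20 × I / (G − 3.5)

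**Step 2: which reading fits the neighbouring formula.** Assume that both indices are scaled so that a reference subject has HOMA-IR = 1 and HOMA-B = 100. This convention is an assumption; the article does not state it. HOMA-IR = 1 means I × G = 22.5, so I = 22.5 / G.

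- Bracketed: 20 × 22.5 / G = 100 × (G − 3.5), that is G² − 3.5 G − 4.5 = 0. The only positive root is G = (3.5 + √30.25) / 2 = (3.5 + 5.5) / 2 = 4.5, and then I = 5.
- Printed: 450 / G² − 3.5 = 100, so G = √(450 / 103.5) ≈ 2.1.

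The bracketed form returns round reference values and a plausible fasting glucose; the printed form does not. At I = 5 and G = 4.5, B = 100 / 1.0 = 100, whereas P = 100 / 4.5 − 3.5 = 18.7.

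**Step 3: size of the error.** The relative shortfall is

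1 − P / B = 3.5 / G + 3.5 × (G − 3.5) / (20 × I)

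It depends on glucose and on insulin. For G = 8 and I = 10: 0.4375 + 15.75 / 200 = 0.516, or 52%.

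| G (assumed) | I (assumed) | Printed | Bracketed | Printed too low by |
|---|---|---|---|---|
| 5 | 5 | 16.5 | 66.7 | 75% |
| 7 | 5 | 10.8 | 28.6 | 62% |
| 7 | 10 | 25.1 | 57.1 | 56% |
| 8 | 10 | 21.5 | 44.4 | 52% |
| 10 | 10 | 16.5 | 30.8 | 46% |
| 10 | 20 | 36.5 | 61.5 | 41% |
| 10 | 30 | 56.5 | 92.3 | 39% |
| 12 | 15 | 21.5 | 35.3 | 39% |
| 15 | 20 | 23.2 | 34.8 | 33% |
| 15 | 30 | 36.5 | 52.2 | 30% |

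Over G of 5 to 15 and I of 5 to 30 the shortfall runs from 30% to 75%. Over G of 7 to 10 and I of 5 to 20 it runs from 41% to 62%, so about half.

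**Step 4: effect on change.**

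- From I = 15, G = 10 to I = 12, G = 8. Printed: 300 / 10 − 3.5 = 26.5, then 240 / 8 − 3.5 = 26.5, a change of 0.0. Bracketed: 300 / 6.5 = 46.2, then 240 / 4.5 = 53.3, a change of +7.2 (before rounding, 53.33 − 46.15).
- From G = 9 to G = 8 with I held at 12. Printed: 23.2 to 26.5, or +14%. Bracketed: 43.6 to 53.3, or +22%.

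**The case against.** Several points can be made on the other side.

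- **The slip may be only typographical.** The article cites a source for the method, and nothing shows that the analysis program follows the printed string rather than that source. This stands: the harm is conditional. A lost layout on text extraction is less likely, because the brackets around the units in the same sentence survived.
- **The dimensional argument is not a proof.** HOMA-B is an empirical index, and its factor 20 carries implied units as well. The reference-value check also rests on a convention that the article does not state. Both points are fair. Still, the two arguments are separate and agree, and nothing in the article favours subtracting 3.5 from the quotient.
- **The outcome ranks low.** Beta-cell function is explanatory. The group comparisons described under Sample size considerations and statistical methods are for primary and secondary outcomes, and the sample size rests on HbA1c alone. The error is also reversible, because HOMA-B can be recomputed from the collected insulin and glucose values. This stands and limits the severity.

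A reader might infer that values computed as printed are always wrong by half or more. The arithmetic does not support that. Since the shortfall always exceeds 3.5 / G, it is above half at every insulin level only up to G = 7. At G = 10 and I = 12 it is 44% (20.5 against 36.9), and at G = 15 and I = 20 it is 33%. Nor does the article support an inference that the trial's beta-cell results were in fact computed wrongly.

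**Conclusion.** The formula is wrong as written. It is a stated computing rule for a listed outcome, it lacks the brackets around glucose minus 3.5, and no other part of the article corrects it. This is not a detail left to an analysis plan that is not shown, because the article itself fixes the formula.

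Followed literally, it understates HOMA-B by roughly 30% to 75%. Those limits rest entirely on the assumed glucose and insulin ranges. Because the shortfall varies with both inputs, it can shrink or hide a change, as in the example where a rise of 7.2 appears as zero.

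Severity is minor: the consequence is confined to one explanatory outcome, arises only if the printed form was programmed, and can be undone by recalculation.

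**What to change.** Print the formula as HOMA-B = 20 × I / (G − 3.5), with I the fasting insulin in μU/ml and G the fasting glucose in mmol/L. Confirm that the analysis program uses this form by checking it against one worked value, for example I = 10 and G = 8, which should return 44.4 and not 21.5. If the printed form has already been used, recompute HOMA-B from the insulin and glucose values.

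The bracketed form is undefined at G = 3.5 and negative below it. A missing-value rule for glucose of 3.5 mmol/L or lower is therefore sensible but optional, and can be left to the analysis plan.

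The cost is one pair of brackets and one program check. No data collection, sample size or primary analysis changes.

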### Physical measurements

Patients above 60 years of age perform a 6 minutes walk test in an indoor unobstructed corridor. They are instructed by a physical therapist to walk the 30 meter from one end to the other at their own pace, as many times as possible, in the permitted time. After 6 minutes, the total distance walked (in meter) is measured. The 6 minute walk test is a useful measure of functional capacity, targeted at older people and people with moderate-to-severe physical impairment and has well known reference equations [32,33].

For patients below 60 years of age physical fitness is measured by using a submaximal cycle ergometer aerobic fitness test (Astrand-Rhyming Cycle Ergometer Test). Patients cycle on an ergometer at a constant workload for 6 minutes. Heart rate is measured every minute, and based on the steady state heart rate, VO_2 _max (correlation to VO_2 _max approximately 0.85–0.9) is determined from a nomogram [34,35].

All participants perform a strength test that involves the determination of the maximum weight that can be lifted 5 repetitive times by arms and legs while maintaining proper form (5RM test) [36]. Self reported daily physical activity (average hours per week in the last 6 months) is divided into: 1) Transportation exercise: walking and bicycling and 2) Training exercise: jogging, training in a fitness centre, swimming, bicycling, etc[36].

### Quality of life questionnaires

Short Form Health Survey (SF-36) is a multi-purpose, short-form health survey with 36 questions. It yields an 8-scale profile of functional health and well-being scores as well as psychometrically-based physical and mental health summary measures and a preference-based health utility index. The SF-36 has proven to be useful in surveys of general and specific populations, comparing the relative burden of diseases, and has been used to differentiate the health benefits produced by a wide range of different treatments [37]. A higher score on SF-36 indicates an improvement in Quality of Life.

Diabetes Symptom Checklist – Revised (DSC-R) is a self-report questionnaire of 34 questions grouped into 8 symptom subscales measuring the occurrence and perceived burden of diabetes-related symptoms [38]. It has been described to be valid, reliable and responsive to change and to be the only scale that appears to evaluate physical functioning in T2DM patients in a broad, comprehensive manner [39]. A lower score on DSC-R indicates an improvement in Quality of Life.

### Sample size considerations and statistical methods

The size of the study population is based on the primary outcome measure HbA1c and is estimated on the basis of the results of two meta-analyses relating to education and exercises in T2DM patients [8,14]. According to power calculation, an absolute difference of 0.7% in HbA1c between the groups (power 0.9, significance level 0.05) may be detected with 80 patients in each group. This calculation is based on a standard deviation of the HbA1c-value of 1.3 from larger population studies [40].

Neither patients nor study personnel are blinded to treatment assignment. The study statistician carrying out the data analysis on the primary and secondary outcomes will be blinded and will not have any contact with the patients.

Descriptive statistics (means ± SD, or median and interquartile ranges, as appropriate) will be used to describe the study sample with regards to baseline characteristics. The analysis will be performed according to the intention-to-treat principles using the statistical software SAS 9.1. Comparisons of primary and secondary outcomes between the two groups will be analyzed by values after the intervention at the 6 months follow-up visit, and 12 and 24 months after baseline, using appropriate parametric tests for variables fulfilling the normal distribution criteria or appropriate non-parametric tests for variables not fulfilling the normal distribution criteria. Sensitivity analyses will be carried out with adjustment for possible confounders. When relevant the change in outcomes from baseline to 6, 12 and 24 months follow-up will be assessed. The proportion of patients reaching the recommended goals for glycated haemoglobin, blood pressure and lipids will be compared in a sub-analysis. Statistical significance is set at P < 0.05.

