## Methods/design

### Patient recruitment and randomization

We plan to recruit patients through advertisements in local newspapers, pharmacies and from the outpatient clinic at Bispebjerg University Hospital, and by letters and e-mails to general practitioners inviting them to refer patients to the study (Figure 1). Key inclusion and exclusion criteria are shown in Figure 2. Diagnosis of T2DM is defined according to the criteria of WHO [18]. Patients willing to participate will be screened after written informed consent is obtained, and those fulfilling the inclusion criteria will be randomised within three weeks, stratified by gender and age (18–54 years and ≥ 55 years). A person not participating in the study creates a randomization list, and the randomization is done at the baseline visit using consecutively numbered sealed envelopes. Patients will be randomised to a group-based rehabilitation programme (intervention group) at the Health Care Centre Oesterbro or to an individual counselling programme (control group) in the Diabetes Outpatient Clinic, Bispebjerg University Hospital.

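### The main HbA1c comparison leaves out baseline HbA1c and the stratification factors: it is valid and adequately powered, but gives up precision and keeps part of any chance baseline difference

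*Protocol article*

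**What the plan says.** Under *Outcome measures and data collection* the protocol article states: "The primary outcome measure is glycosylated haemoglobin (HbA1c". It adds: "All outcome measures are collected at baseline and at follow-up visits after 6, 12 and 24 months". A baseline HbA1c is therefore planned for every patient. Under *Patient recruitment and randomization*, allocation is "stratified by gender and age (18–54 years and ≥ 55 years").

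The analysis is set out under *Sample size considerations and statistical methods*. The between-arm comparisons "will be analyzed by values after the intervention at the 6 months follow-up visit, and 12 and 24 months after baseline". The test depends on the distribution: the article plans on "using appropriate parametric tests for variables fulfilling the normal distribution criteria", and on non-parametric tests otherwise. Two further sentences follow. One places adjustment for confounding variables, which it does not list, in sensitivity analyses. The other reads: "When relevant the change in outcomes from baseline to 6, 12 and 24 months follow-up will be assessed". Baseline HbA1c, gender and age group are not named in any of these.

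The only covariate that the article names is change in medication (*Pharmacological treatment*). It arises after randomisation, and the article does not say which analyses will include it.

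**The concern.** The article states this main comparison outright, so it is not a detail left to an analysis plan. The sample size agrees with it, because it uses the standard deviation of the HbA1c value and not that of a change or of a residual.

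A patient's HbA1c before treatment normally tells something about the value six or more months later. A comparison that ignores it counts that predictable variation as noise, and the interval is wider than the collected data require. If the arms happen to differ at baseline, part of the difference carries into the estimated effect with nothing in the main analysis to remove it. Leaving the stratification factors out also tends to make the standard error somewhat conservative.

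Precision and robustness of the primary result are at stake. The validity of the test is not.

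**Working it through.** **Inputs from the article** (*Sample size considerations and statistical methods*): "an absolute difference of 0.7% in HbA1c between the groups"; "power 0.9, significance level 0.05"; SD of HbA1c 1.3; 80 patients per group. **Assumed:** two-sided test, equal arms, the same SD at baseline and follow-up, and a baseline-to-follow-up correlation r of 0.3, 0.5 or 0.7.

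**1. The plan's own figure.** For an unadjusted comparison of two means, n per arm = 2 × [1.3 × (1.960 + 1.282) / 0.7]² = 72.5, so 73 (74 with the t distribution). The stated 80 is not reproduced exactly but lies on the safe side. At 80 per arm, SE = 1.3 × √(2/80) = 0.2055, and power is 0.926 (0.923 with the t distribution). The 95% half-width is 1.96 × 0.2055 = 0.40.

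**2. Adjusting for baseline HbA1c.** The residual SD is 1.3 × √(1 − r²), so the variance falls by the fraction r². SE = residual SD × √(2/80), half-width = 1.96 × SE, and the difference detectable with 90% power is 3.242 × SE.

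| r (assumed) | Residual SD | SE | 95% half-width | Power for 0.7 | Detectable difference | n per arm for 90% power |
|---|---|---|---|---|---|---|
| unadjusted | 1.300 | 0.2055 | 0.40 | 0.926 | 0.67 | 73 |
| 0.3 | 1.240 | 0.1961 | 0.38 | 0.946 | 0.64 | 66 |
| 0.5 | 1.126 | 0.1780 | 0.35 | 0.976 | 0.58 | 55 |
| 0.7 | 0.928 | 0.1468 | 0.29 | 0.9975 | 0.48 | 37 |

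The table uses the normal approximation. The t distribution adds one patient per arm to the last column.

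**3. Chance baseline difference.** The baseline difference between arms has SE 0.2055. The probability that it exceeds 0.3 points in either direction is 2 × [1 − Φ(0.3 / 0.2055)] = 0.144. At 90 per arm (the 180 in the Abstract, split equally) the SE is 1.3 × √(2/90) = 0.194 and the probability is about 0.12. On average the unadjusted estimate moves by r times the baseline difference. A difference of 0.3 shifts it by 0.09, 0.15 or 0.21 at r = 0.3, 0.5 or 0.7, which is 13%, 21% or 30% of the 0.7 target.

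**4. Change scores are not a safe substitute.** Their variance relative to follow-up values is 2(1 − r): 1.4, 1.0 and 0.6 at the three correlations. With baseline adjustment the ratio is 1 − r²: 0.91, 0.75 and 0.51, which is lower each time.

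**5. Gender and age group.** The article gives no figure linking either factor to HbA1c, so their gain cannot be computed.

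**The case against.** The planned comparison is sound. Over repeated randomisations it is unbiased, its standard error already allows for chance imbalance, and the sample size uses the matching SD. Power is about 92% at 80 per arm. The gain rests on a correlation that the article does not give, and at r = 0.3 it is modest (0.40 to 0.38). Ignoring the strata errs on the side of caution. All of this stands, and it limits the point to efficiency and robustness.

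A reader might infer more than the article supports:

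- **That testing visit by visit breaks intention-to-treat.** The article commits to intention-to-treat and does not say that only attenders are analysed. How missing values are handled may be in the full protocol or analysis plan, which are not shown.
- **That the most favourable analysis can be picked.** The article gives an order: follow-up values first, adjusted analyses as sensitivity, change as an addition. The choice of test follows the distribution and not the result, and the statistician is blinded.
- **That the whole of any baseline difference enters the result.** Only about r times it does, on average.
- **That the model needs a random effect for the treatment groups.** That is a separate question, and nothing in this point establishes it.

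The sensitivity and change analyses do not answer the point. Neither is the main comparison, and neither names baseline HbA1c or the strata.

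**Conclusion.** The point holds as a recommended improvement to a valid and adequately powered analysis. Adjusting for baseline HbA1c would narrow the 95% half-width from 0.40 to about 0.38, 0.35 or 0.29, and would remove the shift of about r times any chance baseline difference. These sizes assume 80 analysed patients per arm, SD 1.3 at both time points, a linear relation, and r of 0.3, 0.5 or 0.7. The correlation may differ between the 6-, 12- and 24-month visits. Any gain above zero correlation comes from data that the trial already plans to collect. Including gender and age group aligns the analysis with the randomisation, but its effect on precision is unknown and may be small.

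**What to change.** Pre-specify one linear model as the main analysis of HbA1c. It can be an analysis of covariance at each visit, or a repeated-measures mixed model over 6, 12 and 24 months with visit and arm-by-visit terms. Either should include arm, baseline HbA1c, gender and age stratum. Report adjusted mean differences with 95% confidence intervals.

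Keep the unadjusted comparison of follow-up values and the change-score comparison as supportive analyses. Keep medication change out of the main model, because it occurs after randomisation and may itself respond to treatment.

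The cost is wording: no extra measurements, patients or visits are needed. If an analysis plan already specifies such a model, the published description should be brought into line with it.

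### The goal-attainment sub-analysis names no baseline term; adjusting for the baseline value already collected would make a valid comparison more precise

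*Protocol article*

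**What the plan says.** The section on sample size and statistical methods gives one sentence to this analysis: "The proportion of patients reaching the recommended goals for glycated haemoglobin, blood pressure and lipids will be compared in a sub-analysis". It names no visit, test, model or covariate, and does not say how a patient already at goal on entry is classified.

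The goals are set elsewhere:
- HbA1c (Biochemical measurements): "The target for haemoglobin A1c is below 6.5% according to international guidelines".
- Blood pressure (Physiological measurements): "Patients' target blood pressures are at the recommended goal of 130/80 mmHg".
- Lipids (Biochemical measurements): "fasting total cholesterol below 4.5 mmol/L and fasting LDL cholesterol below 2.5 mmol/L".

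The sentences just before the sub-analysis set the general approach. For the main outcomes: "Comparisons of primary and secondary outcomes between the two groups will be analyzed by values after the intervention at the 6 months follow-up visit", and likewise at 12 and 24 months. Adjustment follows as a secondary step: "Sensitivity analyses will be carried out with adjustment for possible confounders". Baseline enters only conditionally: "When relevant the change in outcomes from baseline to 6, 12 and 24 months follow-up will be assessed". The data for a baseline term will exist, because the outcomes section says: "All outcome measures are collected at baseline and at follow-up visits after 6, 12 and 24 months".

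**The concern.** A patient's HbA1c, blood pressure or lipid value at entry can be expected to predict whether that patient is at goal later. Cutting a continuous measure at a threshold already discards information; comparing the resulting proportions without the baseline value leaves more prognostic information unused. Randomisation is stratified by gender and age only, so a chance imbalance in entry values stays in the crude difference. It does not bias the comparison over repeated trials, but it adds noise to the one trial that is run.

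There is also a point of wording. *Reaching* a goal suggests movement towards it. Unless defined otherwise, the proportion also counts patients who were at goal from the start. What is at stake is the precision and clear reading of a supporting result.

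**Working it through.** **1. The plan's own figure.** The plan gives no sample size for goal attainment, only for mean HbA1c: difference 0.7, SD 1.3, power 0.9, significance level 0.05, 80 per group. The two-sided normal formula gives

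n = 2 × (1.960 + 1.282)² × 1.3² / 0.7² = 72.5, so 73 per group (74 with the t distribution).

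The stated 80 is on the safe side. At 80, the standardised difference is 0.7 / (1.3 × √(2/80)) = 3.41, and power is Φ(3.41 − 1.96) = 0.93. This figure is not in dispute; it supplies the effect, SD and group size used below.

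**2. Share already below 6.5% at entry.** The article gives no baseline mean, so 7.0, 7.5 and 8.0% are assumed, with no entry limit on HbA1c:
- Φ((6.5 − 7.0)/1.3) = 0.35
- Φ((6.5 − 7.5)/1.3) = 0.22
- Φ((6.5 − 8.0)/1.3) = 0.12

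**3. Simulation for the HbA1c goal.** Baseline B is normal with mean μ and SD 1.3. Follow-up is Y = μ + r(B − μ) − 0.7 × arm + e, where e has SD 1.3√(1 − r²). At goal means Y < 6.5. There were 80 patients per group and 1,500 trials per setting. The correlation r is assumed to be 0.5 or 0.7. The crude analysis is the two-proportion z test. The adjusted analysis is the test of arm in a logistic model with arm and continuous baseline HbA1c. A third analysis drops patients already at goal at entry.

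| Assumed mean | r | Crude power | Adjusted power | Gain (points) | Only those not at goal at entry |
|---|---|---|---|---|---|
| 7.0% | 0.5 | 0.76 | 0.83 | 7 | 0.63 |
| 7.0% | 0.7 | 0.74 | 0.89 | 15 | 0.68 |
| 7.5% | 0.5 | 0.74 | 0.80 | 6 | 0.64 |
| 7.5% | 0.7 | 0.74 | 0.87 | 13 | 0.70 |
| 8.0% | 0.5 | 0.63 | 0.69 | 6 | 0.57 |
| 8.0% | 0.7 | 0.62 | 0.75 | 13 | 0.60 |

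A separate run agreed: crude 0.73–0.74 against adjusted 0.81–0.89 at a mean of 7.2%, and 0.65–0.68 against 0.72–0.80 at 8.0%. Allowing for simulation error (standard error of a single power near 0.75: √(0.75 × 0.25/1500) ≈ 0.011), the gain is about 5 to 15 points.

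**4. Validity.** With no treatment effect, simulated type I error was 0.046–0.055 for the crude test and 0.036–0.052 for the adjusted one over the same means and correlations. Neither is inflated.

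**5. Who is counted.** In the six settings above, 30% to 59% of patients at goal at follow-up had been below 6.5% at entry.

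**6. If entry excluded low HbA1c.** With an assumed mean of 7.5% before truncation and r = 0.6, a floor of 6.5% gives 0.77 crude against 0.81 adjusted, and a floor of 7.0% gives 0.75 against 0.78. Nobody is at goal at entry, and the gain is about 3 to 4 points.

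Blood pressure and lipids were not simulated, because the article gives neither SDs nor effects for them. The simulated model did not include gender and age stratum.

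**The case against.** The strongest objection is that silence is not a decision. A reader might infer that the plan has chosen to ignore baseline; the text does not say so. This is a condensed article, and a model for a sub-analysis may well be set out in the full protocol or analysis plan. The same paragraph foresees adjusted sensitivity analyses and change from baseline, and the section on pharmacological treatment foresees medication changes as a covariate. This stands as a limit on the point: what can be said is that no baseline term is named here and that the general approach puts unadjusted follow-up values first.

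A reader might also infer that many patients will already be at goal. That cannot be checked: no baseline distribution is given, and eligibility is in Figure 2, which was not available to this review. An HbA1c entry limit would remove the issue of patients already at goal for that measure, though not necessarily for blood pressure or lipids, and some gain from adjustment would remain.

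Third, the proportion at goal is a legitimate outcome, and staying at goal is a relevant result. Randomisation balances entry status in expectation, and the test's error rate already allows for chance imbalance. All of this is correct. It answers a charge of bias, which is not made here, but it does not answer the loss of precision.

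**Conclusion.** The point holds as a minor improvement. As described, the sub-analysis is valid, but it names no baseline term although the baseline values will be in hand. For the HbA1c goal, adjustment is worth about 5 to 15 points of power under the assumed means and correlations with no entry limit, and about 3 to 4 points if patients below 6.5 or 7.0% were excluded at entry. The direction is the same throughout; the size rests on those assumptions. For blood pressure and lipids, no size is claimed.

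The documents do not support the stronger readings that the comparison is biased or that the trial's main result is at risk. Type I error is held, the trial is sized on mean HbA1c, and no power is claimed for goal attainment.

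**What to change.** Reword the sentence on the sub-analysis along these lines:

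- Define the outcome as the proportion of patients at goal at each follow-up visit (6, 12 and 24 months), rather than the proportion *reaching* it.
- Compare arms for each goal by logistic regression with arm, the continuous baseline value of the same measure, gender and age stratum.
- Report the standardised risk difference with its 95% CI.
- Tabulate the number at goal at baseline in each arm.
- Exclude nobody on baseline goal status. Restricting to patients not at goal at entry is no remedy: in every setting in the table it gave lower power than the crude comparison.

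If the full protocol or analysis plan already specifies this, a short statement to that effect is enough. The change is to wording only and uses data already being collected; it needs no extra patients, visits or measurements.
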